#### Methods of recruitment

2.3.5

To recruit participants for the clinical study, advertisements will be placed in the mass media, including flyers and daily newspapers, as well as on bulletin boards and websites of the participating institutions. If recruitment is delayed, additional local advertisements will be implemented through subways, busses, apartment bulletin boards, clinical study websites, and applications. All recruitment methods were approved by the IRB and pre-specified in the study registration.

### Intervention and comparisons

2.4

The intervention will be conducted using a two-phase approach. During the premenstrual period (7 days prior to the onset of menstruation), participants will perform daily LLLT through home-based self-administration after receiving standardized training and device instructions. The same intervention protocol, including device settings and application procedures, will be applied during both home-based and on-site administration to ensure consistency of treatment delivery.

The home-based phase is intended to provide repeated therapeutic exposure, whereas each on-site visit is designed as a standardized assessment session under controlled conditions, including biosignal acquisition.

At each menstrual onset, participants will attend a scheduled on-site visit, where LLLT will be administered under investigator supervision. During these visits, biosignals will be collected before, during, and after stimulation to assess physiological responses to the intervention.

In both groups, LLLT is delivered simultaneously to the designated acupoints during each 20-min session. To ensure comparability between the groups, the intervention protocols were designed to provide equivalent dosing. In both groups, stimulation is applied to two acupoints per session, with identical treatment duration (20 min), identical device settings (including wavelength and power density), and comparable irradiation area per acupoint. Consequently, the energy delivered per acupoint and the total energy delivered per session are equivalent across the groups.

Biosignal assessments are conducted as exploratory outcomes under standardized on-site conditions.

#### Local acupoints group (abdominal, near the uterus area)

2.4.1

LLLT will be applied to the local acupoints CV4 (Guanyuan, “Gate of Origin”) and CV6 (Qihai, “Sea of Qi”) in the Conception Vessel. CV4 is located on the anterior midline of the lower abdomen, 3 cun inferior to the umbilicus, while CV6 is located 1.5 cun inferior to the umbilicus on the same line (Figures 2A,B). These acupoints are traditionally used to regulate menstruation and alleviate gynecological and lower abdominal pain (15, 21, 22). They were selected based on their widespread clinical use in the treatment of dysmenorrhea. Each session will last for a total of 20 min, with LLLT applied at CV4 and CV6, using a device emitting 610-nm red light. The intervention will be administered daily for 7 days prior to menstruation across three cycles.

**Figure 2 fig2:**
[figure not shown]
Selected acupoints of local group **(A,B)** and distal group **(C)**.

#### Distal acupoint group (lower limb, systemic regulation)

2.4.2

LLLT will be applied to the distal acupoint SP6 (Sanyinjiao, “Three Yin Intersection”). SP6 is located on the medial aspect of the lower leg, 3 cun above the medial malleolus and posterior to the medial border of the tibia (Figure 2C). This acupoint is traditionally associated with the regulation of menstruation and relief of lower abdominal pain and is widely used in gynecological practice, particularly for dysmenorrhea (23, 24). It was selected as the representative distal acupoint in this study. In the distal group, each session will last for 20 min, during which bilateral LLLT will be delivered to both left and right SP6 acupoints, resulting in stimulation at two acupoints per session, using a device emitting 610-nm red light. The intervention will be administered daily for 7 days prior to menstruation across three cycles.

#### Interventional device

2.4.3

The interventional device to be used in this study is the Color DNA-WSF (Color Seven Co., Ltd., Seocho-gu, Seoul, South Korea), which has obtained authorization under the Korea Good Manufacturing Practice (KGMP, No. 3491) (25). This interventional device has been approved as a medical device by the Ministry of Food and Drug Safety (approval no.: 12–1,367, 26 October 2012).

The technical specifications of the device are as follows:Operating time: 20 min per sessionOutput wavelength: 610 nm ± 10%Output power density: 1.8 mW/cm^2^ ± 20%Output mode: continuous waveIrradiation area (hole size): Ø 4.4 mm ± 10%

This device will be used to deliver LLLT at specified acupoints according to the study protocol.

In both groups, each treatment session lasts for 20 min and is administered once daily for 7 consecutive days prior to the expected onset of menstruation across three menstrual cycles. In the local acupoint group, LLLT is applied to CV4 and CV6, whereas in the distal acupoint group, LLLT is applied bilaterally to SP6 using a 610-nm red light-emitting device.

In both groups, LLLT is delivered simultaneously to two designated acupoints during each 20-min session. Each acupoint is irradiated using an independent light source with identical output parameters, such as wavelength, power density, and irradiation area. Given that energy delivery is determined by power density, irradiation area, and exposure time, and these parameters are identical for each acupoint, the energy delivered per acupoint is equivalent across the groups.

As both groups receive simultaneous stimulation at two acupoints with identical device settings and treatment duration, the number of irradiation sites, per-acupoint dose, and total energy delivered per session are matched. This design minimizes potential confounding due to differences in dose distribution and enables a more direct comparison of stimulation location (local versus distal).

Participants are informed that the perceived sensation of stimulation may vary depending on individual sensitivity. To promote adherence, all treatment sessions are scheduled in advance, and participants receive reminders prior to each visit. Adherence is monitored by recording attendance at each session and documenting completion of the assigned treatment according to the study protocol.

### Multimodal biosignal acquisition

2.5

Biosignals will be measured during three consecutive periods at each hospital visit: a 5-min baseline recording prior to light stimulation, a 20-min recording during the light therapy session, and a 5-min recording immediately after the intervention.

Biosignals will be collected using a system consisting of a biosignal acquisition unit, a laptop computer, and dedicated software. The biosignal acquisition unit is designed to simultaneously record six physiological signals: respiration (RSP), electrocardiogram (ECG), photoplethysmography (PPG), electrodermal activity (EDA), skin temperature (SKT), and electromyography (EMG). Each signal will be measured through specific acquisition modules connected to the MP160 data acquisition system (BIOPAC Systems Inc., Goleta, CA, United States). Wireless transmission will be supported by three Bionomadix® wireless units (BIOPAC Systems Inc., Goleta, CA, United States), which allowed for real-time data transfer to the laptop computer. Data collection and management will be performed using AcqKnowledge® software (BIOPAC Systems Inc., Goleta, CA, United States).

### Randomization, allocation, and blinding

2.6

Participants who meet the eligibility criteria will be randomly assigned in a 1:1 ratio to either the local group (LLLT at CV4 and CV6) or the distal group (LLLT at bilateral SP6).

The random allocation sequence will be generated by an independent statistician using a computer-based random number generator in R software (R Foundation for Statistical Computing, Vienna, Austria) without stratification. A restricted randomization method with block randomization will be used. To minimize predictability, the block size will not be disclosed and will be kept in a separate document inaccessible to investigators responsible for participant enrollment and assignment.

Allocation concealment will be ensured using sequentially numbered, opaque, and sealed envelopes prepared by a researcher not involved in participant recruitment or intervention assignment. Investigators responsible for enrolling participants and assigning interventions will not have access to the random allocation sequence.

Due to the distinct anatomical locations of the interventions, participant blinding is not feasible. Therefore, the study will be conducted with blinding of outcome assessors and statisticians, while clinicians delivering the intervention will not be blinded. Outcome assessments will be performed by independent assessors unaware of group allocation, and statistical analyses will be conducted using blinded group codes.

Emergency unblinding will be permitted only if a participant experiences severe, unrelieved pain or requests withdrawal. All instances of unblinding will be documented, and the participant will be withdrawn from the intervention.

Written informed consent will be obtained from all participants prior to enrollment, and the clinicians will administer the assigned intervention according to the group allocation.

### Sample size

2.7

As this study is an exploratory pilot trial, the sample size was determined primarily based on feasibility considerations and the need to obtain preliminary estimates for a future confirmatory randomized controlled trial, rather than to test a definitive efficacy hypothesis. We therefore did not base the sample size on a formal power calculation. A total of 60 participants, with 30 participants per group, was considered appropriate for evaluating key feasibility parameters, including recruitment, adherence, retention, safety, and completion of outcome assessments. This sample size was also expected to provide preliminary estimates of treatment effect and variability, which will be used to inform the design and sample size calculation of a future adequately powered confirmatory trial. Allowing for an anticipated dropout rate of approximately 20%, the target enrollment was set at 60 participants in total.

### Outcomes

2.8

#### Primary outcome

2.8.1

The primary outcome is the change from baseline in menstrual pain intensity measured using a 0–100-mm VAS (26). The primary endpoint is defined as the change from baseline in VAS measured at the scheduled post-menstrual visit occurring within 3 days after the onset of menstruation, assessed across three menstrual cycles.

A visit window of up to 3 days after menstruation onset is allowed to accommodate inter-individual variability in the timing of peak pain and to ensure feasibility while minimizing protocol deviations. Assessments will be conducted at baseline and at each post-menstrual visit (visit window: day 1 + 3 days) over three menstrual cycles.

To further characterize individual pain patterns, VAS scores will be recorded daily from 7 days prior to menstruation through the first 3 days of menstruation. Sensitivity analyses will be conducted using alternative outcome definitions, including the maximum VAS during menstrual days 1–3.

To evaluate treatment effects, a linear mixed-effects model (LMM) will be used, with treatment group, visit (time point), and group-by-visit interaction specified as fixed effects, and participant-level variability included as a random effect. Baseline VAS will be included as a covariate (27).

#### Secondary outcomes

2.8.2

The secondary outcomes include changes in biosignals and patient-reported outcomes, such as the Korean version of the Beck Depression Inventory-II (K-BDI-II) (28), the EuroQol 5-Dimension 5-Level (EQ-5D-5L) (29), the Stress Response Inventory-Short Form (SRI-SF) (30, 31), and the State–Trait Anxiety Inventory (STAI) (32) assessed at baseline and at each post-menstrual visit (visit window: day 1 + 3 days) over three cycles. PGIC will be assessed once at the final visit (33).

Multimodal biosignals: Multimodal biosignals will be acquired at baseline and at each post-menstrual visit over three menstrual cycles, including RSP, ECG, PPG, EDA, SKT, and EMG. Biosignal measurements will be analyzed as exploratory outcomes. The underlying hypothesis is that stimulation at different acupoint locations may induce differential modulation of physiological responses. Given the exploratory nature of these analyses, no formal adjustment for multiple comparisons will be applied, and the findings will be interpreted as hypothesis-generating.

K-BDI-II: The K-BDI-II is the validated Korean translation of the Beck Depression Inventory-II, a widely used self-reported measure of depressive symptoms. It consists of 21 items, each scored on a 4-point Likert scale (0–3), reflecting symptom severity over the past 2 weeks. Total scores range from 0 to 63, with higher scores indicating more severe depressive symptoms. Standard cutoff scores are defined as minimal (0–13), mild (14–19), moderate (20–28), and severe (29–63).

EQ-5D-5L: The EQ-5D-5L is a standardized instrument for assessing health-related quality of life. It comprises five dimensions: mobility, self-care, usual activities, pain/discomfort, and anxiety/depression. Each dimension is rated on five levels (from no problems to extreme problems). Responses are converted into a single index score using country-specific value sets, with higher scores indicating better health status. In addition, the EQ-5D-5L includes a visual analog scale (VAS; 0–100) for self-rated overall health.

SRI-SF: The SRI-SF is a validated short-form instrument used to assess multidimensional stress responses. It consists of 22 items scored on a 5-point Likert scale (0–4), covering emotional, somatic, cognitive, and behavioral domains. Total scores range from 0 to 88, with higher scores indicating greater stress response levels.

STAI: The STAI is a self-report measure used to evaluate anxiety. It consists of 40 items divided into two subscales: state anxiety (20 items), assessing transient anxiety, and trait anxiety (20 items), measuring general anxiety disposition. Each item is rated on a 4-point Likert scale, with subscale scores ranging from 20 to 80. Higher scores indicate greater levels of anxiety.

PGIC: The PGIC is a single-item measure assessing a patient’s overall perception of change following treatment. It is rated on a 7-point Likert scale ranging from 1 (significantly improved) to 7 (worse response). It is widely used as a global measure of perceived treatment effectiveness.

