Medical and treatment history (including medication use)	●							
Physical examination	●							
Vital signs	●	●		●		●		●
Anthropometrics	●							
Laboratory tests (blood)^a^	●							
Pregnancy test	●							
Visual analog scale (VAS) for pain	●	●		●		●		●
Beck Depression Inventory-II (K-BDI-II)	●	●		●		●		●
Inclusion/exclusion criteria	●							
Allocation								
Randomization		●						
Intervention^b^								
Home-based LLLT at local acupoint (self-administration, daily for 7 days premenstrual)			●		●		●	
On-site LLLT at local acupoint				●		●		●
Home-based LLLT at distal acupoint (self-administration, daily for 7 days premenstrual)			●		●		●	
On-site LLLT at distal acupoint				●		●		●
Assessment								
Quality of life (EQ-5D-5L)		●		●		●		●
Stress response inventory-short form (SRI-SF)		●		●		●		●
State–trait anxiety inventory (STAI)		●		●		●		●
Device dispensing and training for home-based self-administration		●						
Clinical device return								●
Analgesic use check (type and dose)		●		●		●		●
Menstrual diary (distribution/collection)		●		●		●		●
Multimodal biosignal measurements^c^				●		●		●
Compliance with home-based LLLT				●		●		●
Patient Global Impression of Change (PGIC)								●
Changes in medical/treatment history		●		●		●		●
Adverse events				●		●		●
End of study/case closure								●

^a^If laboratory test results within 2 weeks prior to screening are available, they may be used in place of repeat testing at screening. Tests include complete blood count (CBC), liver function tests [such as total bilirubin, total protein, albumin, aspartate transaminase (AST), alanine transaminase (ALT), alkaline phosphatase (ALP), and gamma-glutamyl transferase (GGT)], renal function (such as BUN and creatinine), thyroid function (TSH), and HbA1c. ^b^Low-level light therapy will be performed as home-based self-administration once daily for 20 min during the 7 days prior to menstruation, followed by a single on-site supervised session at each cycle visit. Participants will record light therapy adherence and pain levels in the provided diary. ^c^Multimodal biosignal measurements (on-site only: pre−/during/post-stimulation). Biosignal monitoring will include six parameters: respiration (RSP), electrocardiogram (ECG), photoplethysmography (PPG), electrodermal activity (EDA), skin temperature (SKT), and electromyography (EMG). SPIRIT, Standard Protocol Items: Recommendations for Interventional Trials.

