#### Analysis populations

2.9.1

The analysis populations will consist of the full analysis set (FAS) and the per protocol set (PPS). The FAS will include all randomized participants who receive at least one application of the investigational device and have at least one post-baseline assessment and will be used for primary efficacy analyses in accordance with the intention-to-treat (ITT) principle. The PPS will include participants without major protocol deviations and with a treatment compliance rate of at least 70% and will be used for supportive analyses.

Missing data will be handled within the LMM and generalized linear mixed-effects model (GLMM) using maximum likelihood estimation under the missing-at-random assumption, which allows valid inference without explicit imputation.

In addition, sensitivity analyses will be conducted using multiple imputation to assess the robustness of the results to different missing data assumptions.

No interim analyses are planned.

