#### Between-group comparisons

2.9.3

The primary endpoint, defined as the change from baseline in the VAS measured at the scheduled post-menstrual visit occurring within days 1–3 after menstruation onset, will be analyzed using an LMM. Fixed effects will include treatment group, visit (time point), and the group-by-visit interaction, with baseline VAS included as a covariate. Analgesic use will also be included as a covariate to adjust for its potential confounding effect on pain outcomes. Analgesic exposure in the primary analysis will be defined based on use within a predefined time window prior to VAS assessment. Cumulative analgesic use during the assessment period will be considered in sensitivity analyses. Participant-level variability will be modeled as a random effect.

For secondary outcomes, continuous variables, such as biosignal measures and patient-reported outcomes, will be analyzed using LMMs, and binary or ordinal outcomes, such as PGIC, will be analyzed using the generalized linear mixed-effects models (GLMMs), with treatment group, visit, and group-by-visit interaction specified as fixed effects and participant-level variability as a random effect.

Biosignal analyses will be conducted as exploratory outcomes, and the findings will be interpreted as hypothesis-generating.

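### PGIC is rated only at Visit 4, so its planned likelihood analysis describes Visit 4 attenders and cannot draw on earlier data from women who leave

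*Protocol article*

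**What the plan says.** All references are to the protocol article.

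- **Timing.** Section 2.8.2: "PGIC will be assessed once at the final visit". Table 1 has one mark for PGIC, in the Visit 4 close-out column, and shows no early-termination column.
- **Model.** Section 2.9.3: binary or ordinal outcomes, "such as PGIC, will be analyzed using the generalized linear mixed-effects models (GLMMs), with treatment group, visit, and group-by-visit interaction", plus a participant random effect. Baseline VAS and analgesic use are named as covariates for the primary endpoint; no covariate is named for PGIC.
- **Missing data.** Section 2.9.1 handles missing values in both the linear and the generalized mixed models "using maximum likelihood estimation under the missing-at-random assumption, which allows valid inference without explicit imputation". It then adds that "sensitivity analyses will be conducted using multiple imputation to assess the robustness of the results to different missing data assumptions". The outcomes to be imputed and the variables to be used are not named.
- **Analysis set.** Section 2.9.1 admits to the full analysis set any randomised woman with at least one device application and one post-baseline assessment.
- **Expected loss.** Section 2.7 sets 60 women (30 per group), allowing for dropout of about 20%.

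**The concern.** The missing-data argument in Section 2.9.1 suits an outcome measured repeatedly. A woman who leaves after Visit 2 still informs the VAS analysis, because her Visit 2 value is in the model and is correlated with the values she did not give. PGIC has no earlier value. The same woman is in the full analysis set but supplies nothing to the PGIC likelihood.

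Loss related to outcome is plausible here. Participants know which site is treated, and Section 3.3 accepts that expectation and reporting bias may follow. Section 2.6 links severe unrelieved pain, or a request to withdraw, to withdrawal from the intervention. PGIC asks about the very thing that may drive such exits. Section 2.7 says the trial will supply preliminary effect and variability estimates for a confirmatory trial, so a distorted PGIC result could carry forward into that design.

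**Working it through.** **1. What the model can use.** With a single scheduled visit, the visit factor has one level. The visit effect cannot be separated from the intercept, nor the interaction from the group effect, and one reading per woman gives no meaningful basis for a participant variance. What remains is a comparison of PGIC by arm among women who have a rating. Missing-at-random in that model means that, given arm, missing Visit 4 is unrelated to PGIC. For VAS the same words condition on Visit 2 and 3 values as well, which is a much weaker demand.

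**2. Numbers.** The article gives no power calculation to reproduce. Its dropout allowance is consistent with 48 evaluable women: 48 / (1 − 0.20) = 60. If every dropout misses Visit 4:

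| Dropout | Rated, total | Rated per arm | Unrated per arm |
|---|---|---|---|
| 10% | 54 | 27 | 3 |
| 20% | 48 | 24 | 6 |
| 30% | 42 | 21 | 9 |

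At 20%, the standard error of a group difference grows by √(30/24) = 1.118, about 12%. That is the whole cost if loss is random.

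**3. Bounds.** Assume PGIC is dichotomised and half of the rated women respond in each arm: 12 of 24. If all six unrated women respond in one arm and none in the other, the rates are 18/30 and 12/30, so the difference can lie anywhere from −20 to +20 percentage points. At 10% and 30% dropout the limits are ±10 and ±30. These are extremes, not expectations.

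**4. Size of a plausible bias.** The check was a simulation of 4,000 trials with 30 women per arm. All its inputs are assumptions: a continuous PGIC score in SD units (higher is worse), correlation 0.75 with an earlier visit's score, and dropout that is either random (20%) or increases with a worse earlier score (log-odds −1.6 plus the earlier score, about 21%). The PGIC-only analysis was compared with one that fills in missing PGIC from the earlier score.

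| Scenario | True difference | PGIC only | Using earlier score |
|---|---|---|---|
| Random loss, both arms | 0 | 0.004 | 0.003 |
| Score-driven, same in both arms | 0 | 0.004 | 0.004 |
| Score-driven, same in both arms | 0.50 | 0.46 | 0.50 |
| Random in one arm, score-driven in the other | 0 | 0.13 | 0.00 |

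Differences are absolute values in SD. Simulation error is roughly √(2/24) / √4000 = 0.0046, so 0.003 and 0.004 are indistinguishable from zero. In the second row, each arm's own mean was about 0.13 SD too favourable although the difference was unaffected. In the third row the shared mechanism produced unequal dropout, 14% versus 21%, because one arm did better.

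**The case against.** The strongest reply is that the plan already contains a remedy. Section 2.9.1 adds multiple imputation, and VAS, K-BDI-II, EQ-5D-5L, SRI-SF and STAI are all collected at Visits 2 and 3. The simulation itself shows that using an earlier score removes the bias when dropout depends on that score. This stands in part. A reader might infer that the whole plan yields only a completers' result; the documents do not support that. What is established concerns the main PGIC analysis. The imputation is a sensitivity analysis, it is not stated to include PGIC, and its details may lie in an analysis plan not shown.

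Second, the claim of valid inference is made conditional on missing-at-random, so it is not formally false. That is fair. The difficulty is how much the condition must carry when nothing but arm is in the model. The visit terms may also be generic wording for a class of outcomes, but PGIC is the example named.

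Third, several stronger readings do not hold:

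- *That women who stop early are never rated.* This rests on the schedule shown. The full protocol may provide for ratings at withdrawal, and Section 2.6 does not say that withdrawal from the intervention ends follow-up.
- *That 12 ratings will be missing.* The 20% is a planning allowance for dropout, not a count of missed Visit 4 ratings.
- *That both arms must look better than they are.* Under random loss there is no bias.
- *That a real difference would be hidden.* One can construct this: with 60% of stayers and 10% of leavers improved, and dropout of 10% versus 30%, true rates are 0.6×0.9 + 0.1×0.1 = 55% and 0.6×0.7 + 0.1×0.3 = 45%, while both arms report 60%. Nothing in the documents supports those rates.

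Last, a single rating after three cycles is a sensible definition of PGIC, the outcome is secondary in an unpowered pilot, and Section 2.2 puts the comparison between arms ahead of absolute efficacy. All of this stands and limits the weight of the point.

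**Conclusion.** The point holds for the main PGIC analysis. A single Visit 4 rating, in a model with no earlier outcome, restricts the result to Visit 4 attenders: about 48 of 60 on the assumption that the anticipated 20% dropout all miss that visit. The result is unbiased only if missing Visit 4 is unrelated to perceived change within each arm.

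If women who perceive less benefit leave more often, arm-level ratings look too favourable. The group difference is biased if the dropout mechanism differs by arm, and attenuated if a true difference exists. Under the assumed simulation these effects are 0.13 SD, 0.13 SD, and 0.50 shrinking to 0.46 SD; other correlations or mechanisms would give other figures. The terms for visit, interaction and participant also do not suit an outcome measured once. This is a modest weakness in a secondary outcome and does not touch the primary VAS analysis.

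**What to change.** 1. Ask the PGIC item at the last contact of any woman who stops early, in person or by telephone. Keep the Visit 4 rating as the main result, and do not carry the early rating forward in its place.
2. Analyse PGIC with an ordinal model for a single time point, without visit, interaction or participant random-effect terms.
3. State that the planned multiple imputation covers PGIC, using Visit 2 and 3 VAS, the other patient-reported scores and any early-stop rating.
4. Report the number without a Visit 4 PGIC by arm.

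The cost is one seven-point question for the few women who stop, one schedule amendment, and a short revision of the analysis text. The other scores are already collected. The drawback is that an early-stop rating reflects fewer treated cycles, which is why it should inform the imputation and not replace the Visit 4 value.
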